#### Anxiety symptoms

The Generalized Anxiety Scale-7 (GAD-7) [32] is a 7-item scale that measures symptoms of anxiety over the past two weeks. Each item is responded to using a 4-point Likert scale, and total GAD-7 scores range from 0 to 21. The GAD-7 has demonstrated excellent internal consistency (*α* = .92) [32].

#### General psychological distress

The Kessler Psychological Distress Scale-10 (K-10) [33] is a 10-item scale used to assess nonspecific psychological distress-related symptoms over the past four weeks. Response options span a 4-point scale ranging from “none of the time” to “all of the time,” and total scores range from 0 to 40. The K-10 has demonstrated high internal consistency (*α* = .78) [33].

#### Alcohol consumption

The Alcohol Use Disorder Identification Test – Consumption (AUDIT-C) [34] is a 3-item short-form of the full AUDIT that only measures alcohol consumption. Using a cut-off score of 3, the AUDIT-C has sensitivity of 98% and specificity of 57% for identifying active alcohol abuse or dependence [34].

#### Program evaluation

The Internet Evaluation and Utility Questionnaire (IEUQ) [35] is a 15-item scale used to measure participants’ experiences and perceptions of the online self-directed workbook. Questions include those related to ease of use, convenience, engagement, mode of delivery, and likelihood of returning. The IEUQ has demonstrated adequate internal consistency (*α* = .69) [35].

#### User data

In addition to the measures described above, user data will also be collected from the workbook website. These data will allow us to examine how much time participants spend on the site and individual modules, as well as which modules are in progress or completed, and the number of times participants logged on to access the online workbook.

#### Additional help-seeking

Upon completion of the treatment, participants will be asked to indicate whether or not they will seek further treatment or support for their gambling problems. They will also be asked to indicate what type, if any, that they intend on seeking. Options will include engagement in face-to-face therapy, attendance of support groups, and speaking to family or friends.

### Blinding

Participants will be informed during the consent process that they will be randomly assigned to one of the two intervention conditions. Neither intervention condition will be described as superior. Baseline assessment will occur prior to randomization and follow-up assessments will occur after. Motivational interview sessions will be conducted after randomization, so both participants and interviewers will be aware of participant assignment.

### Data monitoring

A data monitoring committee (DMC) is not necessary for this trial because it (a) poses minimal risk of research-related harm; (b) is unblinded; (c) involves a single data collection site; and (d) does not involve conflicts of interest. The research team, under the guidance of the CFREB, have the responsibility to monitor safety, efficacy, and validity throughout the conduct of the study. The trial will not be audited.

### Sample size estimation

The sample size was determined based on previous work exploring self-directed gambling interventions [11–14] and was computed using G*Power [36] on the basis of H1–H3. The estimation method was based on a repeated-measures between-factors ANOVA, which serves as a simpler derivative of the general linear model that the primary analyses will be based on [37, 38]. Two superiority hypotheses using three primary outcome measures will be analyzed using conventional two-tailed tests with thresholds of power = .80 and *α* = .05. Bonferroni corrections will be calculated to account for multiple comparisons. Correlations of *r* = .50 between baseline and follow-up data were accounted for [16]. A sample size of 108 participants per group will permit statistical detection of small effect sizes (Cohen’s *d* = 0.20 for continuous measures) at the specified significance level. This translates to differential detection of approximately 2 days less gambling per month and a 1-point decrease in NODS scores [37]. After accounting for 20% attrition over 12 months, the resulting planned sample size is 270 participants.

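### With the ANOVA, alpha and correlation the protocol names, 108 per group gives 39–47% power for d = 0.20, not 80%, and less after the planned Bonferroni correction

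*Protocol article*

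**What the plan says.** All the inputs stand in one paragraph of the protocol article, Sample size estimation.

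- Method: "The estimation method was based on a repeated-measures between-factors ANOVA", computed in G*Power.
- Error rates: "conventional two-tailed tests with thresholds of power = .80 and *α* = .05".
- Multiplicity: "Two superiority hypotheses using three primary outcome measures will be analyzed", and "Bonferroni corrections will be calculated to account for multiple comparisons". The divisor is not given.
- Correlation: r = .50 "between baseline and follow-up data were accounted for".
- Result: "A sample size of 108 participants per group will permit statistical detection of small effect sizes", with Cohen's d given as "0.20 for continuous measures) at the specified significance level".
- Clinical translation: "This translates to differential detection of approximately 2 days less gambling per month", and one point on the NODS.
- Attrition: 20%, giving 270 in total.

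The paragraph does not give the number of measurements used. The schedule has baseline and 3, 6, 12 and 24 months, the last added by amendment. H1–H3 predict a larger reduction with the motivational interview, and Data analyses plans GEE to compare the groups on change over time.

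**The concern.** Two groups of 108 are few for a standardised difference of 0.20, and a correlation of .50 between repeated measures does not make up the shortfall in a between-factors test. The article prints the method, alpha, power, correlation, effect size and n together, so the claim can be checked without any further document.

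The figure tells readers which effects the trial could reasonably find. If power at d = 0.20 is 46–47%, the chance of missing that effect is 53–54% instead of 20%, about 2.7 times the stated risk. The equivalents in gambling days and NODS points depend on the same d.

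**Working it through.** **Inputs.** From Sample size estimation: d = 0.20, r = .50, two-sided alpha .05, 108 per group (N = 216). For two equal groups f = d/2 = 0.10. Assumed, because not stated: number of measurements m = 2 to 5 (4 or 5 match the schedule), and a Bonferroni divisor of 3 (2 and 6 also shown).

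**Attrition.** 216/0.8 = 270. This reproduces.

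**Named method.** Noncentral F on 1 and 214 degrees of freedom, with λ = f²·N·m / (1 + (m − 1)r). For m = 4: 0.01 × 216 × 4 / 2.5 = 3.456.

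| m | λ | alpha .05 | .05/2 | .05/3 | .05/6 |
|---|---|---|---|---|---|
| 2 | 2.88 | 39.4% | 29.0% | 23.9% | 17.0% |
| 3 | 3.24 | 43.3% | 32.6% | 27.2% | 19.7% |
| 4 | 3.456 | 45.7% | 34.7% | 29.2% | 21.4% |
| 5 | 3.60 | 47.2% | 36.1% | 30.5% | 22.5% |

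The stated 80% is not reproduced. By this method it needs 493 (m = 4) or 473 (m = 5) analysable participants at .05, and 658 or 632 at .05/3.

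**Other analyses at a true d = 0.20, r = .50, 108 per group.** For the last four rows the variance V is in SD² units and SE = √(2V/108).

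| Analysis | V | alpha .05 | .05/3 |
|---|---|---|---|
| Named method, one-sided .05 | – | at most 60% | – |
| One follow-up, or change to one follow-up | 1 | 31% | 18% |
| One follow-up, adjusted for baseline | 0.75 | 40% | 24% |
| Change from baseline to mean of four follow-ups | 0.625 + 1 − 2(0.5) = 0.625 | 46% | 30% |
| Mean of four follow-ups, adjusted for baseline | 0.625 − 0.25 = 0.375 | 67% | 50% |

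**Settings that come near 80% at N = 216.** None is the named method with d = 0.20.

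- Within-between interaction module, λ = f²·N·m/(1 − r), with f = 0.10 entered: m = 2 at .05 gives λ = 8.64 and 83%; m = 3 at .05/3 gives 81%. In that module f = 0.10 is a difference in change of 0.40 SD (m = 2, where f = δ/(4 SD)) or 0.42 SD (m = 3). A true difference in change of 0.20 SD gives about 31% at .05 and 17% at .05/3.
- Between-factors with f = 0.15, that is d = 0.30: 79% (m = 4) and 81% (m = 5) at .05.

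**Effect detectable with 80% power, 108 per group.**

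| Contrast | alpha .05 | .05/3 |
|---|---|---|
| Named method, m = 4 or 5 | d about 0.30 | 0.34–0.35 |
| Change to mean of four follow-ups | 0.30 | 0.35 |
| Baseline-adjusted mean of four follow-ups | 0.23 | 0.27 |

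**Clinical translation.** If d = 0.20 equals 2 days and 1 NODS point, the implied SDs are 2/0.20 = 10 days and 1/0.20 = 5 points. On those SDs, d = 0.35 is 3.5 days and 1.75 points.

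**Contrast.** A between-factors test compares the groups on their average over all occasions, including the pre-randomization baseline. H1–H3 and the GEE concern the difference in change.

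**The case against.** The strongest reply is that the wrong module was named: a within-between interaction with f = 0.10 does give 80% or more, and m = 3 at .05/3 needs 212 participants, close to 216. That could be how 108 arose, and it would mean that the correction had been allowed for. It does not rescue the sentence, because the effect detected would then be about 0.4 SD of difference in change, not d = 0.20.

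Four stronger readings are tempting, and the document supports none of them.

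- **That the calculation ignored the Bonferroni correction.** The paragraph names alpha .05 and a planned correction, but does not say which alpha was entered. What can be said is that this is unclear.
- **That the source of the error is known.** Several different settings come near 216, so any account of it is conjecture.
- **That the planned analysis has the 67% power of the best case.** Data analyses adds primary outcome variables as covariates only where the groups differ significantly at baseline. Routine baseline adjustment is not planned.
- **That the protocol claims a null result would exclude small effects.** It makes no such statement; the risk lies in how the power figure is read.

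It is also fair that m and the divisor are assumptions here, that the SDs of 10 and 5 are back-calculated from a translation whose source is not at hand, and that allocation, data collection and the primary analysis are unaffected. None of this brings power to 80%. With all 270 analysed and no attrition, the named method gives 54–56% (m = 4 or 5) at .05.

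**Conclusion.** The claim is wrong as printed. At the stated alpha, correlation and n, power for d = 0.20 by the named method is 39–47% over two to five measurements, and 46–47% for the scheduled four or five. With an assumed divisor of three it is 24–31%. For four or five measurements, divisors of two and six give about 35–36% and 21–23%. The exact figure depends on m and the divisor, but the conclusion does not: every analysis examined with a true d = 0.20 and 108 per group falls short of 80%. The named test is also not the contrast that the hypotheses and the GEE address. This is a misstatement of the detectable effect; it does not by itself require a larger trial.

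**What to change.** Keep N = 270 and rewrite the paragraph.

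1. State the G*Power module, the effect-size entry, the number of measurements and the alpha used, including the Bonferroni divisor.
2. Give the effect detectable with 80% power at the corrected alpha for the planned GEE contrast of change over time. By the named method with four or five measurements, d is about 0.30 at .05 and 0.34–0.35 at .05/3. Change from baseline to the mean of four follow-ups gives about the same (0.30 and 0.35).
3. Quote the smaller values (about 0.23 and 0.27) only if the plan is changed to adjust for baseline in every primary analysis.
4. Restate the gambling-day and NODS equivalents with explicit SDs and their source.

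The cost is one paragraph and a less favourable printed figure. No extra participants are needed.

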### Participant recruitment and randomization

Participants will be recruited via targeted internet advertisements (i.e., “Are you concerned about your gambling? Study includes free and confidential online help for your gambling”). These advertisements will be distributed online (e.g., Facebook; Kijiji; YouTube; Google; Twitter; Reddit) to media users across Canada. To meet inclusion criteria, participants must (a) be a Canadian resident; (b) be 18 years of age or older; (c) have gambled at least once within the last month; (d) score 5 or more on the Problem Gambling Severity Index (PGSI) [20]; and (e) not currently be involved in treatment for their gambling. As with most prior gambling intervention trials, use of psychiatric medication will not be an exclusion criterion, but will not be assessed or monitored in this study. Prospective participants will be excluded if they are unable or unwilling to (a) provide their phone number and email address or (b) access the online program to create an account.

Individuals who are interested will be automatically redirected from a social media advertisement to an online eligibility screening questionnaire on Qualtrics. Those who are found to be ineligible will be thanked for their interest and directed to alternative resources for gambling help without any contact from the research team. Those who meet eligibility criteria will be automatically prompted to provide consent and contact information within Qualtrics, and then complete the baseline assessment. Qualtrics will be monitored daily for completed surveys that meet eligibility criteria and indicate consent. Eligible participants will be randomized by the research team to one of the two treatment groups and notified of their group assignment via email. Those selected to receive a motivational interview will also be invited to schedule their session. As previously mentioned, participants will not receive the initial compensation until the aforementioned steps have been completed. Those who complete at least one but not all of these steps will be sent a maximum of two reminder emails. Eligible participants can choose to be informed of the trial results via email upon its completion. Regardless, any publications and presentations resulting from this trial will be agreed upon by all investigators.

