##### Gambling severity

In addition to gambling frequency and expenditures, gambling severity will also be assessed. The NODS [28] is a 17-item measure that uses DSM-IV criteria to assess gambling problems. The 3-month version of the NODS has been previously validated as an outcome measure for gambling intervention research, demonstrating good internal consistency (*α* = .87) [29]. It also correlates highly with other measures of gambling severity (*r* = .86) and moderately with number of days gambled and number of dollars spent (*r* = .50) [30].

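### The sample size section pairs d = 0.20 with about 1 NODS point and 2 days; this rests on unstated SDs of 5 points and 10 days and does not fit 108 per group at 80% power

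*Protocol article*

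**What the plan says.** Under Sample size estimation, the protocol article bases its calculation on a between-factors repeated-measures ANOVA in G*Power, with "conventional two-tailed tests with thresholds of power = .80 and *α* = .05" and a correlation of .50 between baseline and follow-up. It states that 108 per group can detect "small effect sizes (Cohen’s *d* = 0.20 for continuous measures"). The next sentence converts this to natural units, with a reference to a cited source: "This translates to differential detection of approximately 2 days less gambling per month and a 1-point decrease in NODS scores". Allowing for 20% attrition, the total becomes 270. The same paragraph says "Bonferroni corrections will be calculated to account for multiple comparisons", without giving the divisor or saying whether it entered the calculation.

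Under Gambling severity (primary outcomes), the NODS "is a 17-item measure that uses DSM-IV criteria to assess gambling problems". The article gives no score range, mean or SD for the NODS, and no SD for days gambled.

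**The concern.** The section gives one effect twice: as a standardised difference, and as differences on two primary outcomes. The two versions agree only if the SDs are 5 NODS points and 10 days. Nothing in the article supports those values, and 5 points is a wide spread for a symptom score in people screened for gambling problems.

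Severity is a primary outcome (H2), and the 1-point figure is the only statement of the difference the trial is meant to detect on it. Readers will judge the severity result, especially a null one, against that figure. If 1 point is not the effect used for sizing, a null result could be read as excluding a difference that the calculation never represented.

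**Working it through.** **Inputs from the article:** d = 0.20; 1 NODS point; about 2 days; 108 per group (N = 216); two-sided α = .05; power .80; r = .50; 20% attrition; 17 NODS items. **Assumptions:** NODS SD of 2 to 5; NODS range 0–10 or 0–17; number of measurements m = 1 to 5.

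**1. The plan's own figures.** Attrition reproduces: 216/0.80 = 270. The 108 per group does not. For two groups f = d/2 = 0.10, and the named between-factors test has noncentrality λ = f²·N·m/(1+(m−1)r). At α = .05 and 80% power it needs total N = 592, 526, 494 and 474 for m = 2, 3, 4 and 5, and more with a Bonferroni correction.

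**2. Implied SDs.** SD = difference/d, so 1/0.20 = 5.0 NODS points and 2/0.20 = 10 days. Taking d on change scores alters nothing: the SD of change is SD·√(2(1−.50)) = SD.

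**3. How wide an SD of 5 is.** The largest possible SD is half the range. On 0–10 that is 5.0, reached only with half the sample at each end. On 0–17 it is 8.5, and an even spread over all scores gives 5.19. So 5 is the mathematical maximum on the first scoring, and very wide but possible on the second.

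**4. What the pairing becomes at other SDs.** Power is for a 1-point difference with 108 per group under the between-factors test at α = .05, from m = 1 to m = 5.

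| Assumed SD | 1 point as d | d = 0.20 in points | Power for 1 point |
|---|---|---|---|
| 2 | 0.50 | 0.4 | 96% to >99% |
| 2.5 | 0.40 | 0.5 | 83% to 97% |
| 3 | 0.33 | 0.6 | 68% to 88% |
| 3.5 | 0.29 | 0.7 | 55% to 77% |
| 4 | 0.25 | 0.8 | 45% to 66% |
| 5 | 0.20 | 1.0 | 31% to 47% |

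**5. Fit with n and power, named test.** The last row is the only one where d = 0.20 and 1 point agree. There λ = 0.01 × 216 = 2.16 for m = 1 (power 31%) and 0.01 × 216 × 5/3 = 3.6 for m = 5 (power 47%). At α = .05/3 these fall to about 18% and 31%. A more favourable analysis, baseline-adjusted with four averaged follow-ups, has variance factor (1+3×.5)/4 − .5² = 0.375. The standard error is then √(2×0.375/108) = 0.083 SD, the ratio 0.20/0.083 = 2.4, and power about 67%.

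The d detectable with 80% power at α = .05 is 0.38 (m = 1) to 0.30 (m = 5). One point therefore reaches 80% power only if the SD is about 2.6 to 3.4, and it is then d = 0.38 to 0.30.

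**6. Fit with n and power, interaction.** For a within-between interaction, λ = f²·N·m/(1−r). With f = 0.10 and m = 2, λ = 0.01 × 216 × 2/0.5 = 8.64. Power is 83%, and N = 200 suffices. But f = 0.10 in a 2×2 layout moves each cell mean by 0.10 SD, so the difference in change is 4 × 0.10 = 0.40 SD. Check: 0.40²/(2/108) = 8.64. One point is then an SD of 1/0.40 = 2.5, and 2 days an SD of 2/0.40 = 5 days. The effect is 0.40 SD, not 0.20.

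**The case against.** A reader might infer that the NODS cannot produce an SD of 5, so the 1-point figure is plainly wrong. The documents do not support this. It needs a 0–10 score, and the article gives only the number of items. On 0–17 the spread is possible without being near-uniform. For example, with 40% of people spread evenly over 0–4 and 60% over 9–15, the mean is 8, the variance is 0.4(2+36) + 0.6(4+16) = 27.2 and the SD is 5.2. Nor does the entry rule settle it: the requirement to "score 5 or more on the Problem Gambling Severity Index (PGSI") restricts another instrument at entry and places no limit on NODS scores at follow-up.

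It can also be said that the translation cites a source not available here, that a condensed article may leave out SDs and score ranges, and that at an SD of 4 the 0.8 points could be rounded to 1. All of this stands, and the missing SDs are not by themselves the finding.

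The strongest objection is that the wording about differential detection, together with the planned analysis of group differences in change, suggests an interaction effect, which also brings N close to 216. On that reading 1 point may be a fair target. But the section names a between-factors test, and the interaction reading saves the 1-point figure only by making the d = 0.20 label wrong.

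**Conclusion.** The point holds in a limited form. The division is consistent: d = 0.20 and 1 point agree if the SD is 5. What fails is the combination of d = 0.20, 1 point, 108 per group and 80% power. With an SD of 5, power for 1 point is about 31% to 47% under the named test, and about 67% under the most favourable analysis checked. Under the two-measurement interaction that does reach 80%, 1 point is 0.40 SD, twice the stated effect. No reading checked makes all four figures true together.

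How far the points figure is out depends on an SD the article does not give. Over assumed SDs of 2 to 4, d = 0.20 is 0.4 to 0.8 points; at 5 there is no gap. The 2-day figure rests on an SD of 10 days, which is possible for a monthly count but equally unsupported. These results assume r = .50, equal variances over time and, except where stated, no Bonferroni correction.

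**What to change.** State which G*Power procedure and effect were used (between-factors or within-between interaction), with f, the number of measurements and the alpha entered. State the NODS score range and the SDs relied on for NODS and days gambled, taken from the earlier workbook trials or from this trial's pooled, arm-blind baseline data. Baseline data can serve for days only if days are recorded, because the outcome description mentions hours. Then either restate the NODS and days differences that d = 0.20 represents, or keep 1 point and 2 days and restate the larger standardised effect they represent. The text should not claim that the scale cannot produce an SD of 5.

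The cost is one or two sentences in the sample size section and a short recalculation. Enrolment, follow-up and conduct are unaffected.

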### Data analyses

All statistical analyses will be conducted using SPSS version 26.0 at 12- and 24-month follow-up time points. Following completion of the 24-month follow-ups, the trial will be terminated. If baseline data are missing completely at random, they will be handled using the full imputation maximum likelihood approach to estimate means, variances, and covariances. Missing data at follow-ups will be handled with the multiple imputation method. Analyses will be conducted using the intention-to-treat (ITT) approach. Bivariate comparisons of all demographics and outcome measures will be conducted to explore differences between groups at baseline. Chi-square tests of independence will be used to compare groups on categorical measures, while *t* tests will be used to compare groups on continuous measures. Any primary outcome variables with significant differences between groups will be controlled for by entering them in as covariates in primary and secondary analyses. It is likely that the primary outcome variables will appear non-normally distributed when assessed with q-q plots and Shapiro-Wilk tests; in these cases, data will be appropriately transformed to achieve normality. If the data transformations are unsuccessful, separate nonparametric analyses will be conducted as appropriate instead of the respective planned analyses outlined below. Additionally, chi-square tests of independence will be used to determine if attrition rates differ in terms of treatment group or baseline characteristics.

H1 and H2 will be analyzed using generalized equation estimation (GEE) to determine if there are group (IO; IMI) differences in change over time. Outcome variables will include gambling frequency (i.e., number of days gambled in the last month), expenditures (i.e., average number of dollars lost per gambling day), and severity (i.e., NODS score). GEE is advantageous because it can account for the natural correlations over time in longitudinal data [38].

To aid in clinical significance and translation, H1 and H2 will also be analyzed categorically with two separate logistic regressions. Both analyses will include Group and Time as binary predictors. The analysis to test H1 will include gambling disorder status (meets criteria; does not meet criteria) as the binary outcome. The analysis to test H2 will include recovery status (abstinence; improvement; no improvement) as the multinomial outcome. Improvement is defined as at least a 50% reduction in average number of dollars lost per gambling session.

H3 will be analyzed with a bivariate Pearson correlation between time spent on the site and change in dollars spent per gambling day from baseline to follow-ups.

H4 will be analyzed with two bivariate comparisons. Two unpaired *t* tests will be conducted to determine if the adherence rates differ by group after the 12- and 24-month follow-ups. Adherence will be measured in two ways: (1) number of modules completed on the program and (2) total time spent on the program website.

To test the exploratory research question, bivariate comparisons will be conducted. Q1 will be analyzed with an unpaired *t* test comparing group treatment ratings at each of the follow-up periods (3, 6, 12, and 24 months).

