Several self-directed interventions for GD have been established [7–9]. Notably, Hodgins and Makarchuk [10] developed a self-help workbook for gambling problems based on cognitive-behavioral principles. The activities within the workbook are organized into four modules: self-assessment, goal setting, goal implementation, and goal maintenance. Among other activities, workbook users are able to assess the frequency and severity of their gambling behaviors, set reduction- or abstinence-based goals, and plan for future urges, triggers, or potential relapses. This particular workbook has demonstrated efficacy in multiple trials [11–14]. The results of these trials suggest that the efficacy of this workbook is maintained even without any therapist contact (e.g., motivational interviewing), although the effects are not as strong.

In the first trial examining the efficacy of Hodgins and Makarchuk’s workbook [10], Hodgins and colleagues [13, 14] randomized participants to one of three trials: workbook-only, workbook plus telephone motivational interview, or a 4-week waitlist control condition. Follow-up assessments were conducted at 1, 3, 6, 12, and 24 months. Results indicated that both the workbook-only and workbook plus motivational interview groups experienced reductions in gambling frequency and severity compared to the waitlist control group at all time points except the 12-month follow-up. The improved outcomes were more substantial for the workbook plus motivational interview group. Although still significant, group differences were smaller at 6- and 24-month follow-ups compared to 1- and 3-month follow-ups [13, 14]. However, since differential gains were still observed at 24 months, the results suggest that the benefits of self-directed interventions are still apparent in the medium- to long-term, particularly when supplemented with a single session of motivational interviewing. Interestingly, a subsequent trial by Hodgins and colleagues [12] observed no incremental improvement in outcomes when additional motivational interviews were provided. These findings imply that a single motivational interview is enough to enhance the benefits of self-directed workbooks, and additional motivational interviews may not be necessary.

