## Methods

### Ethical approval and compensation

This study, including the methods and design, was approved by the University of Calgary Conjoint Faculties Research Ethics Board (CFREB), REB20-0568, in May 2020. Any modifications to the protocol, including changes to the objectives, design, sample size, or study procedures, will be agreed upon by all investigators and submitted for ethical review and approval prior to implementation. As of October 2021, two protocol amendments have been approved and implemented: (a) addition of a 24-month follow-up period to the existing 3-, 6-, and 12-month follow-up plan; and (b) requirement of MI session completion prior to, rather than following, the first CAD $10 compensation.

Participants will be financially compensated an electronic gift card valued at CAD $10 following: (1) confirmation of eligibility; (2) completion of the baseline assessment; (3) creation of an account with the online self-help program; and (4) completion of a motivational interview (if assigned to that group). Participants will also be remunerated with an electronic gift card valued at CAD $30 after each of four follow-up assessments have been completed in full; in total, participants could receive CAD $130 in electronic gift cards. Participants will have the ability to choose electronic gift card(s) from a number of local stores and restaurants. There is a possibility that some participants will sell their gift cards to finance gambling or otherwise take advantage of the compensation offered. We will mitigate this by screening for duplicate participants and using electronic (versus physical) gift cards.

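### Three primary outcomes are each analysed at 12 and again at 24 months with no deciding time point, and conflicting counts of the hypotheses leave the Bonferroni threshold at .025, .0167 or .0083

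*Protocol article*

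**What the plan says.** - **Analysis times.** Data analyses: "All statistical analyses will be conducted using SPSS version 26.0 at 12- and 24-month follow-up time points". The same section plans a GEE of group differences in change over time, without naming the contrast or the time point that decides.
- **Origin of the second time.** Ethical approval and compensation lists as an approved amendment the "addition of a 24-month follow-up period to the existing 3-, 6-, and 12-month follow-up plan".
- **Basis of the sample size.** Sample size estimation: "After accounting for 20% attrition over 12 months, the resulting planned sample size is 270 participants". The calculation "was computed using G*Power [36] on the basis of H1–H3".
- **Size of the family.** The same paragraph goes on: "Two superiority hypotheses using three primary outcome measures will be analyzed using conventional two-tailed tests with thresholds of power = .80 and" alpha = .05. The next sentence reads "Bonferroni corrections will be calculated to account for multiple comparisons". No divisor is given, and the text does not say whether the two analysis times belong to the family.
- **Hypotheses.** H1, H2 and H3 are each a superiority hypothesis for one outcome: frequency, severity and expenditures.
- **Hypotheses as analysed.** Data analyses assigns the GEE to H1 and H2 only, yet lists all three outcomes under it. It then tests H3 as a Pearson correlation between time on the site and change in dollars, which is not a group comparison.

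**The concern.** Two gaps combine. First, each primary outcome gets two full analyses a year apart, and neither is declared decisive. The 12-month results will be known before the 24-month analysis is run, so a deciding time that is not declared could be chosen with data in hand. Second, the statement that should control this, the Bonferroni correction, sits beside counts that disagree: two hypotheses, three outcomes, and H1–H3 (three hypotheses). With two analysis times, a family of six is also possible.

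The divisor changes conclusions. A p-value of .02 on one outcome is a success at .05/2 = .025, and a failure at .05/3 = .0167 or .05/6 = .0083. If the divisor counts only hypotheses or outcomes, the second analysis gives extra chances of a false positive that nothing in the text pays for.

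**Working it through.** **Inputs.** From Sample size estimation: "conventional two-tailed tests with thresholds of power = .80 and *α* = .05"; 108 per group; 20% attrition; r = .50 between baseline and follow-up. From the description of the NODS: r = .50 with days gambled and dollars spent. From Data analyses: three outcomes, two analysis times. Assumed, because the document does not give them: correlation among the outcome test statistics from 0 to .8, and between the 12- and 24-month statistics from 0 to .9.

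**Step 1, the plan's own figure.** 2 × 108 = 216, and 216 / (1 − 0.20) = 270. This reproduces the stated total and shows that it depends on attrition at 12 months.

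**Step 2, candidate thresholds.**
- Two hypotheses: .05/2 = .025
- Three outcomes, or H1–H3: .05/3 = .0167
- Three outcomes × two times: .05/6 = .0083

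**Step 3, six independent tests, all nulls true.** P(at least one false positive) = 1 − (1 − .05/k)^6.
- k = 2: 1 − .975^6 = .141
- k = 3: 1 − .98333^6 = .096
- k = 6: 1 − .99167^6 = .049

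**Step 4, six correlated tests.** Simulation of six two-sided normal test statistics (800,000 draws). The correlation between any two is the product of the outcome correlation and the time correlation that apply to the pair.

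| Outcome r | Time r | k = 2 | k = 3 | k = 6 |
|---|---|---|---|---|
| 0 | 0 | .141 | .096 | .049 |
| .5 | .5 | .119 | .082 | .043 |
| .5 | .7 | .110 | .076 | .040 |
| .5 | .9 | .093 | .064 | .034 |
| .8 | .5 | .094 | .065 | .035 |
| .8 | .9 | .073 | .051 | .027 |

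Rounded, the ranges are 7–14% for k = 2, 5–10% for k = 3 and 3–5% for k = 6.

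**Step 5, sensitivity to the form of the test.** If each GEE is read as an omnibus group-by-time test, run once on the waves to 12 months and again with 24 months added, simulation at correlations of .5 gives .090 (k = 2), .062 (k = 3) and .032 (k = 6). The rates are lower, and the order is the same.

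**Step 6, one deciding time.** Three tests at .05/3: 1 − .98333^3 = .049 if independent, and .045 at outcome correlation .5. Naming one time point therefore holds 5% with a divisor of 3.

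**The case against.** The strongest reply is that the plan does commit to Bonferroni for multiple comparisons and nowhere excludes the analysis times. If the correction covers all six tests, the error rate is controlled. That stands. A reader might infer that the trial's false-positive rate simply is about 8–12%, but the document does not support this. The figure needs the added assumption that the second analysis lies outside the family, and even then it depends on the divisor and on correlations that are mostly assumed. The stated r = .50 over time links baseline with follow-up, not 12 with 24 months.

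A divisor of 2 is also a strained reading. The sentence that counts two hypotheses gives three outcomes in the same breath, and the article elsewhere speaks of four hypotheses where it lists five. This looks like stale numbering rather than an intention to test three outcomes at .025. That is a fair reading, but the text still has to be corrected before anyone can rely on it.

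An exact divisor is commonly left to an analysis plan, which is not shown, and its absence alone would be no finding. Here the protocol states counts that conflict, and an analysis plan would have to override one of them.

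Two further inferences should not be drawn:
- **That the sample size fits no candidate threshold.** This is true only of the named between-factors test. Taking d = 0.20 as f = 0.10 with r = .50, that test needs 474–592 in total at alpha .05 for five down to two measurements. A group-by-time interaction with three measurements at .05/3 needs 212, against the planned 216. But four measurements at .05/6 need 202 and two at .05 need 200. The number of measurements is not stated, so the sample size neither rules out nor identifies the threshold.
- **That the background evidence shows the two times will disagree.** The earlier result, a benefit "compared to the waitlist control group at all time points except the 12-month follow-up", compares active arms with a waitlist. It does not bear on IMI against IO.

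**Conclusion.** The point holds as an ambiguity in the decision rule that should be corrected. Every primary analysis is run at two times with no deciding time or contrast, and the counts that would set the Bonferroni divisor contradict one another. The per-test threshold could be .025, .0167 or .0083.

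The size is conditional. Trial-wide error is held at or below 5% if all six tests share the correction. It exceeds 5% in every setting examined if the second analysis time is left out, though with a divisor of 3 and high correlations only barely (.051). No passage counts six tests or places time in the family, and none excludes it, so the document does not settle which case applies.

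These rates assume that all null hypotheses are true, that the test statistics are approximately normal, and that a success on any one outcome at either time would be claimed as superiority.

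**What to change.** In Sample size estimation, change the count of superiority hypotheses from two to three (frequency, severity, expenditures) and state the family. In Data analyses, assign the GEE to H1, H2 and H3. Name as the deciding contrast for each outcome the IMI-minus-IO difference in change from baseline to 12 months, the time for which attrition was budgeted. Test the three at .05/3 = .0167, or with Holm, which is never less powerful than Bonferroni. Label the 24-month analysis secondary, as durability of effect. The correlation now listed under H3 belongs with the hypothesis on time spent online.

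If the sponsor wants both times to support a superiority claim, state a family of six, at .05/6 = .0083 each or with Holm over six.

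The cost is two or three sentences, with no new data or participants, provided that they are fixed before the 12-month analysis. With the first option, a 24-month result alone could not carry the claim. With the second, each test faces a stricter threshold.
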